### Relevant concomitant care permitted or prohibited in the trial {11d}

Patients will be encouraged not to use any complementary topical treatments on the breast skin for the duration of the trial. Other radiotherapy-related acute toxicities will be treated *lege artis*.

### Provisions for post-trial care {30}

All patients will receive standard follow-up. Due to the excellent safety profile of NIPP, harm from trial participation is not expected.

### Outcomes {12}

#### Clinician-reported outcome (CRO)

Patients will be evaluated during weekly on-treatment visits. Any additional visits requested by the participants will also be documented. RD severity of the irradiated breast will be assessed according to the National Cancer Institute’s Common Terminology Criteria for Adverse Events (CTCAE; version 5.0) [32]. Furthermore, hyperpigmentation, breast oedema, and desquamation (dry or moist) will be assessed and recorded. Upon radiation treatment completion, as well as 2 and 6 weeks later, acute toxicity will be reassessed. An experienced breast radiation oncologist, blinded to the allocation, will perform all clinical assessments. The topical corticosteroid prescription rate (to alleviate radiation dermatitis-related symptoms) will also be assessed in both arms.

#### Patient-reported outcome (PRO)

At the end of the radiation course and during the two follow-up visits, the patient-assessed modified Radiation-Induced Skin Reaction Assessment Scale (RISRAS) will be recorded [33]. All patients will report their maximum breast-related experience of pain, itching, burning, and limitations in daily activities. Items are scored on a 4-point Likert scale: 0 = not at all; 1 = a little; 2 = quite a bit; 3 = very much.

#### Objective assessment

At baseline, during every visit, on the last day of radiation treatment, as well as during both follow-up visits, four skin colour readings will be performed across the irradiated breast (one in each of the breast quadrants) with a reflectance spectrophotometer (CR-10 Plus, Konica Minolta, Tokyo, Japan). This compact device has previously been validated to objectively assess RD in a non-invasive manner [34, 35]. The automatically performed measurements are based on the Commission Internationale de l’Éclairage (CIE) system of tristimulus values. They describe a measured colour in three coordinates using the L*a*b* system: lower L* values describe darker skin (hyperpigmentation) and higher a* values indicate redness or erythema (RD). The b* values describe the position on a scale from blue to yellow and are of secondary importance in the acute setting.

#### Patient-reported experience (PRE)

During the last follow-up visit, patient-reported experiences will be captured through an exit questionnaire with several yes–no statements. To further enhance public and patient involvement, this questionnaire was adapted from the one used in the phase 1 and 2 trial, further refined based on included patient’s feedback.

### Participant timeline {13}

The participant timeline is shown in Fig. 2.

**Fig. 2 Fig2:**
[figure not shown]
Participant timeline. d = day; w = week; NIPP = non-invasive physical plasma; CRO = clinician-reported outcome; PRO = patient-reported outcome; PRE = patient-reported experience

### Sample size {14}

The primary endpoint of this trial is clinician-assessed RD (as per CTCAE v5.0) in the NIPP and placebo group upon radiation treatment completion. The sample size calculation is based on the results of our phase 2 trial [28]. A decrease in mean clinician-reported RD severity upon radiation treatment completion of at least one third will be assumed with NIPP (RD severity with standard skin care: 1.06 ± 0.71 [4]). To detect such a difference (*Δ* = 0.35; standard deviation [SD] = 0.7) with 80% statistical power with a two-tailed *t*-test at a significance level of 5%, an analysed sample size of *n* = 128 is needed (i.e. 64 patients per treatment arm). We plan to analyse the CTCAE severity grades as ordinal data using a non-parametric Mann–Whitney-Wilcoxon test. The required sample size is, however, computed for a parametric test. In order to achieve the same degree of confidence as a similar parametric test, a larger sample size is thus needed for the non-parametric test [36]. As a rule of thumb, sample size will therefore be increased by an additional 10%, resulting in *n* = 140 (i.e. 70 patients per treatment arm). Based on both previous trials, we expect 20% drop-out after initial informed consent (*n* = 168 randomised). Of all patients being referred to our department, we expect 20% meeting inclusion criteria but declining participation (*n* = 202 enrolled and assessed for eligibility).

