**Methods:**

In this randomised double-blind placebo-controlled trial, patients with breast cancer will be randomised (1:1) to receive either 120 s of NIPP or sham treatment with an identical device daily during hypofractionated breast irradiation following breast-conserving surgery. Standard skin care with urea lotion will be applied twice daily to the whole breast by all patients. Acute skin toxicity will be assessed weekly and includes clinician- (CTCAE v5.0) and patient-reported (modified RISRAS), and objective (spectrophotometry) assessments. The trial has started enrolment in the first quarter of 2024 and is projected to recruit 140 patients over 36 months.

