### Interim analyses {21b}

There are no planned interim analyses. The excellent safety profile of NIPP renders an interim safety analysis or stopping rules obsolete. The efficacy of the intervention versus placebo will only be assessed if the preplanned sample size has been reached.

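### The 20% drop-out allowance is applied as 140 × 1.2 = 168 rather than 140/0.8 = 175, so 168 randomised leaves about 134 analysed, and the figures that depend on it need restating

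*Protocol article*

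**What the plan says.** All of this is in the protocol article.

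- **Sample size {14}, base size.** The calculation is for a t-test "with 80% statistical power with a two-tailed" alternative, "at a significance level of 5" per cent, with a mean difference and spread of "0.35; standard deviation [SD] = 0.7". It gives "an analysed sample size of" 128, or 64 per arm.
- **Sample size {14}, rank-test allowance.** Because the primary test is Mann–Whitney–Wilcoxon, the size is raised by 10% as a rule of thumb, to 140 (70 per arm).
- **Sample size {14}, drop-out.** "Based on both previous trials, we expect 20% drop-out after initial informed consent"; the number randomised is given as 168.
- **Sample size {14}, refusals.** Of the patients referred, "we expect 20% meeting inclusion criteria but declining participation"; the number assessed for eligibility is given as 202.
- **Abstract, Methods.** The trial "is projected to recruit 140 patients over 36 months".
- **Interim analyses {21b}.** After saying that no interim analysis is planned, the section adds that efficacy "will only be assessed if the preplanned sample size has been reached". It does not say which number that is.

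**The concern.** The base size of 128 is explicitly a number analysed, and the 10% increase compensates for the choice of test, so 140 is also a number analysed. To have 140 left after losing a fraction d, one randomises 140/(1 − d). The protocol multiplies by (1 + d) instead, which falls short for any d above zero. The randomised number therefore does not deliver the analysed number under the protocol's own drop-out rate.

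Two other places use these numbers. The abstract attaches 140 to recruitment, although the sample size section has 168 randomised. The interim analyses section makes the efficacy assessment conditional on a planned size without saying whether it means 128 or 140 analysed, 140 recruited or 168 randomised. At stake are a modest overstatement of power and an unclear condition on whether and when efficacy is assessed.

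**Working it through.** **Inputs** (Sample size {14} unless noted): difference 0.35, SD 0.7, so d = 0.35/0.7 = 0.5; two-sided 5%; power 80%; rank-test allowance 10%; drop-out 20%; refusal 20%; allocation 1:1 (Sequence generation {16a}).

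**1. Reproduce the plan's figures.**
- Two-sample t-test (noncentral t), d = 0.5: 63.8 per arm, so 64 per arm and 128 in total. This agrees with the protocol.
- 128 × 1.10 = 140.8; the protocol's 140 is close enough.
- 140 × 1.2 = 168. This reproduces the stated number randomised exactly.
- 168 × 1.2 = 201.6, so 202. This reproduces the stated number assessed.

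**2. Apply the stated drop-out.**
- 168 × 0.8 = 134.4 analysed, about 67 per arm and 5 to 6 below 140.
- 140/0.8 = 175; in equal arms, 70/0.8 = 87.5, so 88 per arm and 176 in total.
- The drop-out at which 168 does yield 140 is 1 − 140/168 = 16.7%.
- The drop-out at which 168 still yields 128 is 1 − 128/168 = 23.8%.

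**3. Power.** t-test, d = 0.5, two-sided 5%. The protocol's 10% allowance is represented by an effective size of n/1.1 per arm.

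| Analysed | Per arm | With 10% allowance | Without |
|---|---|---|---|
| 128 | 64 | – | 80.1% |
| 134 to 134.4 | 67 to 67.2 | 78.1% to 78.3% | 81.9% to 82.0% |
| 140 | 70 | 79.9% | 83.6% |

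The loss is about 1.7 percentage points on the protocol's method.

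**4. Number approached.** If 20% of eligible patients decline, 168/0.8 = 210. Starting from 175 it is 175/0.8 = 218.75, so 219; from 176 it is 220.

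**5. The condition on the efficacy assessment.** Take each patient's loss as independent with probability 0.2, so the number analysed from 168 is binomial (168, 0.8).
- P(at least 140 analysed) = 16%.
- P(at least 128 analysed) = 91%.
- With the division done correctly, P(at least 140) is 55% from 175 and 60% from 176, because that calculation meets the target only on average.

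Whether the condition is likely to be met therefore depends on which number is meant. If it means 168 randomised or 140 recruited, drop-out does not affect it.

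**The case against.** **The effect is very small.** About 134 analysed still exceeds the 128 needed for the t-test, and the shortfall of 6 is half of a 12-patient margin that the protocol itself calls a rule of thumb. No endpoint, test or error rate changes. This stands, and it limits the severity.

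**Not every drop-out need leave the primary analysis.** The modified intention-to-treat set excludes only patients who do not start the allocated treatment ({20c}), and data up to withdrawal are used ({18b}). The primary endpoint is at completion of radiotherapy, so losses at the 2- and 6-week visits do not remove it. Drop-out is also counted from consent, so some may precede randomisation. This stands in part: 134 is the yield if the whole 20% is lost between randomisation and the endpoint. But a patient who withdraws before radiotherapy ends has no value at that time point, and the protocol itself inflated as though these patients were lost.

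**The 202 is only a screening forecast.** This also stands in part. The sentence refers to all patients referred and gives no rate of ineligibility, so 210 holds only if the 20% is taken of eligible patients. Inference is unaffected.

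**Two stronger readings that the article does not support.** A reader might infer that the protocol's own rule would leave the completed trial without an efficacy analysis. The sentence stands under the interim analyses heading, where it can be read simply as ruling out an early look, and the size it refers to is undefined. Of the candidate numbers, only 140 analysed makes a miss likely. A reader might also take the abstract's 140 as the number randomised, and so expect far fewer analysed. The sample size section gives 168 randomised explicitly, and 140 matches its analysed requirement, so loose wording is the better explanation.

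**Conclusion.** The arithmetic error is certain: 168 comes from multiplying by 1.2, and under the stated 20% it does not deliver the 140 analysed that the protocol asks for. The shortfall is about 6 analysed patients, or 7 to 8 randomised. It costs about 1.7 points of power on the protocol's own method (79.9% to about 78.2%). This assumes that all of the 20% is lost after randomisation and before the primary endpoint, and it takes the protocol's effect size, SD and 10% allowance as given.

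The abstract's 140 and the number randomised do not agree as worded. The condition in the interim analyses section is undefined; if it means 140 analysed, the stated 168 would probably miss it. That is a reason to define it, not evidence that the analysis would be withheld. Severity: minor to moderate.

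**What to change.** 1. **Sample size {14}.** Either keep 168 and state that 20% drop-out gives about 134 analysed and about 78% power on the protocol's method, or state 175 randomised (176 for equal arms).
2. **Number approached.** Recompute it by division and say what the 20% refusal is a percentage of. If it is of eligible patients, the number is 210 from 168, or 219–220 from 175–176.
3. **Abstract.** Say 140 analysed and 168 randomised, or the revised figures.
4. **Interim analyses {21b}.** State that there is no efficacy look before recruitment and follow-up for the primary endpoint are complete, and that the final analysis is then done and reported whatever number is analysed. A threshold on the number analysed should not decide this, since even 175–176 randomised would reach 140 only a little more often than not.

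Keeping 168 costs wording only, with a stated power slightly below 80% on the protocol's method. Choosing 175–176 adds 7 to 8 patients to recruitment. Either way, make the change as an amendment before the analysis.

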### Recruitment {15}

Based on both previous trials, we expect completion of the trial within 36 months from initiation to be feasible.

#### Assignment of interventions: allocation

### Sequence generation {16a}

Using intrapatient randomisation (the irradiated breast is divided into a lateral and medial half; one breast half receives experimental treatment, while the other breast half receives standard of care or placebo) has proven useful in several trials investigating (acute or chronic) RD management approaches [37–40]. This omits the need for stratification based on known risk factors influencing the RD risk and limits confounding when assessing trial endpoints. The volatile nature of NIPP, however, does not allow such trial design, as potential diffusion to the contralateral (placebo) breast half with a subsequent effect is likely, as was the case in our phase 2 trial [28]. Therefore, a separate control group receiving standard skin care + placebo will be recruited. A 1:1 randomisation (NIPP:placebo) will be undertaken, with patient stratification based on two proven risk factors for RD development and severity: total radiation dose (i.e. presence or absence of a boost to the tumour bed) and irradiated breast volume (as measured in the radiation treatment planning computer tomography: small < 400 mL, medium 400 − 800 mL, large > 800 mL) [35, 41]. Patients will be assigned to intervention or placebo using a stratified block randomisation process (block size will be disclosed upon final publication of the results), using a computer-generated random number list, created by a team member not involved in the clinical part of the trial. Other factors which are known to modulate the RD risk (e.g. body mass index, diabetes mellitus, smoking history, Fitzpatrick skin type) will not be included in the stratification process, but will be documented and presented (including balance between groups).

### Concealment mechanism and implementation {16b} {16bc}

Allocation will be undertaken by a trained radiation oncology nurse who is also the NIPP/placebo device operator. Allocation information will be stored on a password-protected secure server, inaccessible to the blinded investigators.

## Assignment of interventions: blinding

### Who will be blinded? {17a}

Patients and treating physicians will be blinded until completion of the trial for individual patients; only the device operator is aware of the respective allocation and will not be conducting any assessments. Data analysts and statisticians will also be blinded.

### Procedure for unblinding {17b}

Upon trial completion for individual participants, unblinding is performed by the treating radiation oncology nurse, if requested by the patient. Sealed emergency envelopes will be stored at a location known and accessible to all trial personnel and can be used for premature unblinding in emergency situations.

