#### Placebo

Patients randomised to the control arm will receive sham treatment with an identical device, which produces the same sound and feeling, yet does not produce NIPP. To keep the devices separated, they will be marked “1” and “2”. The treating radiation oncology nurse is the only one who will be aware of the exact allocation.

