#### Oversight and monitoring

### Composition of the coordinating center and trial steering committee {5d}

The coordinating center consists of the principal investigator, investigators (all with full delegation), and the involved study nurses. Investigators will recruit and enroll patients in addition to performing the blinded outcome assessments. The unblinded study nurses will perform the administration of the allocated treatment. Five prescheduled investigator meetings are planned during the recruitment period to evaluate progress of the trial or assess any issues that might have arisen.

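### Unblinding patients on request while enrolment continues can expose later patients' subjective primary grades; disclosure should wait for database lock

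*Protocol article*

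**What the plan says.** The section Who will be blinded? {17a} sets the length of blinding per person: "Patients and treating physicians will be blinded until completion of the trial for individual patients". Procedure for unblinding {17b} adds the disclosure route: "Upon trial completion for individual participants, unblinding is performed by the treating radiation oncology nurse, if requested by the patient". The only other route described is premature unblinding by sealed envelope in an emergency. No section ties individual disclosure to the last patient's assessment or to database lock.

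Four other statements bear on this:

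- **Setting.** Study setting {9} names one recruiting department. Trial status gives a 36-month trial.
- **Roles.** The coordinating-centre section {5d} states: "Investigators will recruit and enroll patients in addition to performing the blinded outcome assessments".
- **Device code.** The Placebo section states: "To keep the devices separated, they will be marked". The marks are the numerals 1 and 2. It does not say where the mark sits or who can see it.
- **Allocation.** Sequence generation {16a} states: "Patients will be assigned to intervention or placebo using a stratified block randomisation process". The strata are boost (yes or no) and three breast-volume classes. The block size is withheld until publication.

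The section Sample size {14} defines the endpoint at risk as follows: "The primary endpoint of this trial is clinician-assessed RD (as per CTCAE v5.0) in the NIPP and placebo group upon radiation treatment completion".

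**The concern.** Blinding that ends patient by patient is harmless only if what is disclosed about a finished patient tells nobody anything about patients still to be graded. Here two routes could carry information forward.

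The first is the device code. With two devices and two fixed marks, a single known link between a mark and an arm gives the code for every patient. If marks are visible to patients or assessors, a finished patient who learns her arm and knows her mark can supply that link.

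The second needs no device mark. The investigators who may hear of disclosed allocations also recruit the next patients. In stratified blocks, past allocations carry some information about the next one.

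The endpoint makes this matter. The Discussion itself describes physician grading by CTCAE as subjective, with considerable variability between and within observers. A grade influenced by knowledge of the arm biases the comparison directly, and the analysis cannot remove that bias afterwards.

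**Working it through.** **Step 1. The plan's own figure.** Inputs from Sample size {14}: difference 0.35, SD 0.7, two-sided 5%, power 80%. The standardised difference is 0.35/0.7 = 0.5. The normal approximation gives 63 per arm. The exact t-test solution is 63.77, so 64 per arm and 128 in total, with power 0.801. Adding 10% gives 128 × 1.10 = 140.8, against the stated 140 (70 per arm). The figure reproduces and is not in dispute; SD 0.7 and 70 per arm are used below.

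**Step 2. When disclosure can start.** Radiotherapy takes 15 fractions, or up to 15 + 8 = 23 with a sequential boost. At 5 fractions per week (assumed) that is 3 to 4.6 weeks. The last visit is 6 weeks after radiotherapy, so the first patient can ask at 3 + 6 = 9 to 4.6 + 6 = 10.6 weeks. Her own primary grade was taken at the end of radiotherapy, 6 weeks before that.

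**Step 3. What follows the first permitted disclosure.** Assume uniform accrual of 168 patients, with 36 months (156 weeks) less one patient's course available for accrual: 156 − 9 = 147 to 156 − 10.6 = 145.4 weeks.

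- Rate: 168/147 = 1.14 to 168/145.4 = 1.16 patients per week.
- Randomised before the first permitted disclosure: 1.14 × 9 = 10.3 to 1.16 × 10.6 = about 12.2.
- Primary grade recorded by then: 6 weeks × rate = about 7.
- Share of primary assessments still to come: 1 − 6/147 = 96%.

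The 96% is the share that could be exposed if the first patient to finish asks. It is not the share compromised.

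**Step 4. Effect on type I error.** Assume no true effect, a fraction f of assessments decoded, and a grading difference of b between arms in those assessments. The average shift is f × b. The standard error is 0.7 × √(2/70) = 0.118. The two-sided rejection rate is Φ(fb/0.118 − 1.96) + Φ(−fb/0.118 − 1.96). Both f and b are assumptions; the protocol gives neither. The planned test is Mann–Whitney-Wilcoxon, so these figures are approximate.

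| Decoded share f | Shift b (grade) | Average shift | Type I error |
|---|---|---|---|
| 10% | 0.1 | 0.010 | 5.1% |
| 10% | 0.2 | 0.020 | 5.3% |
| 25% | 0.1 | 0.025 | 5.5% |
| 25% | 0.2 | 0.050 | 7.1% |
| 50% | 0.2 | 0.100 | 13.5% |
| 96% | 0.2 | 0.192 | 36.8% |

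A shift across a whole arm of 0.1 or 0.2 grade gives 13.4% or 38.9% with the t-test.

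**Step 5. Block prediction.** There are 2 × 3 = 6 strata. If they were equal in size (assumed), each would hold 168/6 = 28 patients. During one patient's 9 to 10.6 weeks, 28/147 × 9 = 1.7 to 28/145.4 × 10.6 = 2.0 further patients would enter her stratum. A disclosure could therefore arrive while her block is still filling, but this depends on the block size, which is rightly withheld.

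**The case against.** The strongest reply is that several safeguards are in place and the route to bias is long. Only the nurse who operates the device knows the allocation, and the nurse does no assessments. The allocation file is closed to blinded investigators. A blinded oncologist grades. Data analysts and statisticians are blinded with no per-patient end point. Disclosure happens only if a patient asks, and only after her own follow-up. For a later grade to be affected through the device code, a finished patient must ask, must know her mark, and must pass on both arm and mark. A current patient's mark must then reach the assessor before grading, and the assessor must be swayed. No step has a known probability.

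Most of this stands and limits the point. A reader might infer that patients see the mark daily and that every disclosure decodes everyone else. The documents do not support that. They say the marks keep the devices apart, and nothing about visibility; placement may be covered in the full protocol. A reader might also infer that future allocations become predictable. With the block size withheld, disclosure voluntary and a lag of 9 to 11 weeks, the text supports only that guessing may become easier.

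What does not stand is the idea that these safeguards close the gap. They govern what the nurse and the file reveal. None of them stops a finished patient from telling an investigator or another patient, and section {17a} itself stops blinding the treating physician at that point.

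**Conclusion.** The disclosure rule is set too early for a trial that goes on enrolling and grading at one department. It leaves the disclosed patient's primary grade untouched and puts later patients' grades at avoidable risk. On the assumptions of 5 fractions per week and uniform accrual, most primary assessments fall after the first permitted disclosure.

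The size of any bias cannot be derived from the documents. With 10% to 25% of assessments decoded and a shift of 0.1 to 0.2 grade, type I error moves from 5% to between about 5% and 7%. Rates of 13% or 39% require an average shift of 0.1 or 0.2 grade across a whole arm, which is the worst case and not an expectation. It would go too far to conclude that the primary endpoint is unprotected or that the design fails. The point is a worthwhile, low-cost improvement: the rule should be changed because later patients' grades gain protection and the sample size is unaffected.

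**What to change.** Amend Who will be blinded? {17a} and Procedure for unblinding {17b} so that patients, treating physicians and assessors stay blinded, and individual allocations are withheld, until the last patient's final assessment and database lock. Allow earlier disclosure only through the existing emergency procedure. The blinding of analysts and statisticians needs no change.

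As an added safeguard, amend the Placebo section to replace the two constant marks with several neutral codes per device type, linked to allocation only on the operator's list. One known link would then no longer reveal the arm of every other patient.

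The cost is a short amendment and a set of labels. The downside is that patients wait longer to learn their allocation. As the trial is already enrolling, the change helps only patients not yet assessed, so it is worth making promptly.
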